### Sample size

2.7

A priori power analysis (G*Power 3.1) was conducted for a four-group repeated measures ANOVA (interaction effect). To detect a medium effect size (f = 0.25) with a power of 0.8 and an alpha level of 0.05, a total sample of approximately 128 participants (32 per group) is required. To account for potential participant dropouts, we have factored in an anticipated attrition rate of 20% over the 24-week study period (12-week intervention plus 12-week follow-up). This 20% estimate is intentionally conservative and rigorously justified by previous longitudinal literature involving older adults with cognitive impairment. Systematic reviews of intensive, multi-modal non-pharmacological interventions (including aerobic exercise and neuromodulation protocols) in geriatric populations consistently report attrition rates ranging from 15% to 21%, typically due to transportation barriers, intervention fatigue, or unrelated emergent health issues (Di Lorito et al., 2020). Therefore, to ensure the trial remains adequately powered throughout the follow-up phase, we aim to recruit a final total of 160 participants (40 per group).

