##### Analysis of primary and secondary outcomes

2.9.1.2

To evaluate the individual and synergistic effects of the interventions across the three assessment time points (baseline, Week 12, and Week 24), linear mixed-effects models (LMMs) will be employed. LMMs are particularly well-suited to this trial design, as they accommodate repeated measures, account for intra-subject correlation, and appropriately handle missing data under the missing-at-random (MAR) assumption without necessitating listwise deletion. The outcome measures—including global cognitive function (MoCA), memory, executive function, EEG/ERP parameters, and physical performance metrics—will be modelled as dependent variables. Fixed effects will comprise Group (Combined Intervention, rTMS Only, DMI Only, Control), Time (T0, T1, T2), and the Group × Time interaction term, with the latter serving as the primary indicator of intervention efficacy over the study period. Participant identification will be specified as a random intercept to account for between-subject variability.

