##### Covariates and adjustments for multiplicity

2.9.1.4

The models will be adjusted for pre-specified, clinically relevant covariates, including age, gender, educational attainment, and baseline MoCA scores. Should baseline imbalances be detected across groups despite randomization, the affected variables will additionally be incorporated as covariates. For multiple pairwise comparisons across groups or time points, *post-hoc* analyses will be adjusted using either the False Discovery Rate (FDR) method or the Bonferroni correction to control the family-wise error rate.

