##### Handling of missing data

2.9.1.5

Although LMMs intrinsically accommodate missing data, multiple imputation (MI) via chained equations will be applied as a supplementary sensitivity analysis if the overall missing data rate exceeds 10% (in light of the anticipated 20% attrition rate), thereby corroborating the validity of the primary ITT findings. For all analyses, a two-sided p-value of less than 0.05 will be considered statistically significant.

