### Outcome hierarchy and multiplicity adjustment

2.10

To address concerns about multiplicity, the trial outcomes are organized in a pre-specified hierarchy. The primary outcome is the change from baseline (T0) to post-intervention (T1) in MoCA total score. Three pre-specified key secondary outcomes, all analyzed as T0 to T1 changes paralleling the primary, are: (1) change in executive function, operationalized as the TMT-B/A ratio to control for motor speed, with TMT-B and TMT-A reported separately as supporting analyses; (2) change in P300, assessed by peak latency (ms) and peak amplitude (μV) at midline electrodes (Fz, Cz, Pz); and (3) change in BBS score. To control the family-wise Type I error rate across these three key secondary outcomes, the Holm-Bonferroni step-down procedure will be applied; effect estimates with 95% confidence intervals (unadjusted and adjusted) will be reported, with the adjusted p-values used for inference. T0 to T2 changes (durability) for all three key secondary outcomes, as well as all other pre-specified outcomes—including WMS-IV (memory), 6MWT (functional exercise capacity), SF-12 (quality of life), and rs-fMRI (DMN and frontoparietal connectivity)—are treated as supportive/exploratory and are interpreted with caution.

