## Conclusions

4

We hypothesize that the combined rTMS and DMI group will demonstrate superior and more durable improvements in global cognition and physical performance compared to the monotherapy or control groups. By providing a comprehensive, mixed-methods evaluation of this synergistic approach, this trial aims to inform future clinical guidelines and offer a feasible, culturally appropriate strategy for managing MCI in the aging population.

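### The post-hoc pairwise rule offers FDR as a way to control the family-wise error rate, a property that FDR does not have once some arms truly differ

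*Protocol article*

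**What the plan says.** Section 2.9.1.4 of the protocol article sets the rule for post-hoc tests. "For multiple pairwise comparisons across groups or time points", the results are to be "adjusted using either the False Discovery Rate (FDR) method or the Bonferroni correction to control the family-wise error rate". It gives no rule for choosing between the two methods and does not define the family.

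The general level is in section 2.9.1.5: "For all analyses, a two-sided p-value of less than 0.05 will be considered statistically significant".

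Section 2.10 has a separate multiplicity rule with a limited scope: "To control the family-wise Type I error rate across these three key secondary outcomes, the Holm-Bonferroni step-down procedure will be applied". It does not reach pairwise arm comparisons on MoCA.

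The arm-versus-arm claim is in section 4, which expects the combined arm to show "superior and more durable improvements in global cognition and physical performance compared to the monotherapy or control groups".

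**The concern.** Bonferroni and FDR control different things. Bonferroni bounds the probability of any false rejection in the family. Benjamini-Hochberg bounds the expected share of rejections that are false, and this coincides with the family-wise rate only if there are no real differences at all. Once some comparisons truly differ and are rejected, the thresholds for the remaining true nulls loosen. The sentence therefore promises something that one of its two options does not deliver.

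The stake is the set of arm-versus-arm statements. The hypothesis in section 4 compares the combined arm with each monotherapy and with control. Neither the overall Group × Time test nor the rTMS × DMI interaction shows that arm by arm, so the pairwise comparisons have to carry it.

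**Working it through.** **Inputs from the protocol article.** There are four arms (section 2.9.1.2: "Fixed effects will comprise Group (Combined Intervention, rTMS Only, DMI Only, Control), Time (T0, T1, T2), and the Group × Time interaction term"), hence 4 × 3 / 2 = 6 pairs, 3 of them involving the Combined arm. The level is two-sided 0.05 (section 2.9.1.5). Section 2.7 plans 128 evaluable participants, 128 / 4 = 32 per arm, and recruits 128 / (1 − 0.20) = 160, or 40 per arm.

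**The plan's own figure.** With f = 0.25, λ = f²N = 0.0625 × 128 = 8. A one-degree-of-freedom interaction in a 2 × 2 ANOVA then has power 0.801, so 128 and 160 both reproduce. They matter here only as the source of the arm sizes. The plan gives no numeric family-wise rate for the pairwise tests.

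**Assumed.** FDR means Benjamini-Hochberg. Data are normal with pooled variance. Effects are in SD units and shown as a range, because the article gives no SD for MoCA change.

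**Why the rate moves.** Suppose three of the six comparisons are real and already rejected. The smallest of the three remaining null p-values then faces:
- Benjamini-Hochberg: 4 × 0.05 / 6 = 0.0333
- Holm: 0.05 / 3 = 0.0167
- Bonferroni: 0.05 / 6 = 0.0083

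Multiplying by three nulls gives 10%, 5% and 2.5% as rough sums. Correlation between pairs sharing an arm brings the simulated values down to about 8.4%, 4.3% and 2.2%.

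**Simulation, six pairs, 32 per arm.** Entries are the percentage of trials with at least one false difference. The last column counts only false findings that involve the Combined arm, under FDR. The run used 400,000 replicates per row, except the 1 SD row (100,000).

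| True pattern | FDR | Bonferroni | Holm | FDR, Combined pairs |
|---|---|---|---|---|
| All arms equal | 4.4 | 4.1 | 4.1 | 2.9 |
| Only Combined better, 0.8 SD | 7.1 | 2.3 | 3.5 | 0 |
| Only Combined better, 1 SD | 7.9 | 2.2 | 4.0 | 0 |
| Only Combined better, very large | 8.4 | 2.2 | 4.3 | 0 |
| Combined = both monotherapies > Control, 0.5 SD | 5.1 | 2.2 | 2.8 | 3.9 |
| Same, 0.8 SD | 7.2 | 2.3 | 3.5 | 5.4 |
| Same, very large | 8.5 | 2.3 | 4.4 | 6.4 |
| Only rTMS works, 0.5 SD | 4.8 | 1.7 | 2.3 | 2.4 |
| Only rTMS works, 0.8 SD | 6.6 | 1.7 | 3.2 | 3.4 |
| Only rTMS works, very large | 8.2 | 1.7 | 5.0 | 4.2 |

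With only Combined better, FDR gives 6.8% at 0.75 SD and 8.4% at 1.5 SD. The 40-per-arm results are close to those for 32.

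The zeros in the last column follow from the pattern: if Combined beats every other arm, no Combined comparison is a true null. The 7.9% in that scenario consists wholly of false differences among the other three arms.

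**Direction.** The worst Combined-arm figure, 6.4%, counts errors in both directions. Half of it, 6.4 / 2 = 3.2%, is a false claim that Combined is superior. The nominal figure for one direction is 0.05 / 2 = 2.5%.

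**Three-pair family.** If only the Combined-arm pairs form the family, FDR in that worst pattern gives 4.6% at 0.5 SD, 5.5% at 0.8 SD and 6.2% for a very large effect.

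**Disagreement.** FDR and Bonferroni, each over six pairs, differ on at least one Combined-arm comparison in:
- 25.5% of trials: Combined +0.75 SD, others equal, 32 per arm
- 23.3%: monotherapies +0.4 SD, Combined +0.8 SD, 40 per arm
- 20.5%: Combined +0.5 SD alone, 40 per arm

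In these three scenarios every Combined difference is real, so the disagreement is about detecting it.

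**The case against.** The strongest reply is that these comparisons are labelled post hoc. Section 2.9.1.2 makes Group × Time the main indicator of efficacy, section 2.9.1.3 rests synergy on the rTMS × DMI interaction, and section 2.10 already protects the key secondary outcomes. None of these uses the FDR option, and section 4 states a hypothesis rather than a decision rule. This stands, and it limits the weight of the point.

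A reader might infer that claims of superiority for the combined arm run well above 5%. The figures do not support that. The 7 to 8% is the chance of any false pairwise difference, and in the scenario where only Combined works none of it involves the Combined arm.

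A reader might also infer much larger rates by pooling within-arm time comparisons, with a practice gain on MoCA, into one family with the arm comparisons. That could raise the rate, but section 2.9.1.4 mentions comparisons across groups or time points without saying that they are pooled, and the article states no practice gain. No figure is claimed for it.

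Nor does the text say that the choice between methods waits for the results; an analysis plan not shown here may fix it. An analysis plan that settled on FDR would still be consistent with section 2.9.1.4, however, and the stated property would still be wrong.

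Finally, restating the aim as FDR control, with FDR as the only method, would also make the sentence true. That is a legitimate alternative, but it abandons the family-wise aim that the plan sets itself.

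**Conclusion.** The point holds as an error in a stated rule. One of the two permitted methods does not control the family-wise rate, and the two are not interchangeable. The excess is modest. It is absent when all arms are equal, negligible around 0.5 SD, and two to three percentage points for any false pairwise difference at 0.75 to 1.5 SD. For Combined-arm comparisons it is at most about 1.4 points two-sided (6.4 − 5) in the worst pattern tried.

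These sizes rest on Benjamini-Hochberg, a six-pair family, normal data, assumed effect sizes, and a 5% target taken from the general significance level because section 2.9.1.4 gives none. The sentence should be corrected before analysis, but it does not threaten the trial's main tests.

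**What to change.** In section 2.9.1.4, delete the FDR option and the either-or. Name Holm as the single method, over the between-arm comparisons of T0 to T1 MoCA change, and state that time-point comparisons are kept out of that family. Holm is already used in section 2.10 ("the Holm-Bonferroni step-down procedure will be applied"), controls the family-wise rate whichever nulls are true, and is never less powerful than Bonferroni.

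The cost is one sentence and some power relative to the FDR option; power is gained relative to the Bonferroni option. Sample size, design and the other planned tests do not change.

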##### Handling of missing data

2.9.1.5

Although LMMs intrinsically accommodate missing data, multiple imputation (MI) via chained equations will be applied as a supplementary sensitivity analysis if the overall missing data rate exceeds 10% (in light of the anticipated 20% attrition rate), thereby corroborating the validity of the primary ITT findings. For all analyses, a two-sided p-value of less than 0.05 will be considered statistically significant.

#### Qualitative statistics

2.9.2

Transcribed interview data will be analyzed using thematic analysis, following the six-phase approach outlined by Braun and Clarke (Braun and Clarke, 2006). Data will be coded independently by two researchers, and discrepancies will be resolved through discussion to enhance trustworthiness. NVivo software (Version 14.24.3) will be used to assist with data management and coding. Key themes related to acceptability, feasibility, and perceived impact will be identified and interpreted.

#### Mixed-methods data integration

2.9.3

To maximize the explanatory power of this study, the integration of quantitative and qualitative data will occur at the interpretation phase using an embedded mixed-methods framework. Rather than analyzing the data streams in isolation, the qualitative findings will be systematically used to contextualize, explain, and expand upon the quantitative results. For example, if the quantitative linear mixed-effects models reveal that the Combined Intervention group achieves high clinical efficacy but suffers from unexpectedly low adherence or high attrition rates, the qualitative data will be crucial in identifying the underlying mechanisms—such as the perceived logistical or physical burden of attending both the iTBS and dance sessions. Conversely, if specific cognitive domains (e.g., executive function) show significant improvement, the interview transcripts will be analyzed to uncover the specific components of the DMI or social interactions that participants felt contributed most to those gains. This synergistic integration will provide a comprehensive understanding of not just *whether* the intervention is effective, but *how* and *why* it works, thereby yielding highly actionable insights for future real-world clinical implementation.

### Outcome hierarchy and multiplicity adjustment

2.10

To address concerns about multiplicity, the trial outcomes are organized in a pre-specified hierarchy. The primary outcome is the change from baseline (T0) to post-intervention (T1) in MoCA total score. Three pre-specified key secondary outcomes, all analyzed as T0 to T1 changes paralleling the primary, are: (1) change in executive function, operationalized as the TMT-B/A ratio to control for motor speed, with TMT-B and TMT-A reported separately as supporting analyses; (2) change in P300, assessed by peak latency (ms) and peak amplitude (μV) at midline electrodes (Fz, Cz, Pz); and (3) change in BBS score. To control the family-wise Type I error rate across these three key secondary outcomes, the Holm-Bonferroni step-down procedure will be applied; effect estimates with 95% confidence intervals (unadjusted and adjusted) will be reported, with the adjusted p-values used for inference. T0 to T2 changes (durability) for all three key secondary outcomes, as well as all other pre-specified outcomes—including WMS-IV (memory), 6MWT (functional exercise capacity), SF-12 (quality of life), and rs-fMRI (DMN and frontoparietal connectivity)—are treated as supportive/exploratory and are interpreted with caution.

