Previous studies have demonstrated that rTMS, particularly when applied to the dorsolateral prefrontal cortex (DLPFC), a region critical for executive function and memory, can improve cognitive performance in individuals with MCI (Guo et al., 2025; Yuan et al., 2025). Recent comparative trials indicate that iTBS over the left DLPFC yields cognitive benefits equivalent to conventional high-frequency rTMS in MCI, while requiring only a fraction of the session time (e.g., 3 vs. 37.5 minutes) (Zheng et al., 2024). rTMS can also modulate functional connectivity within key brain networks, such as the default mode network (DMN) and fronto-parietal network, which are often disrupted in MCI (Esposito et al., 2022; Guo et al., 2025). By directly influencing neural circuits and promoting synaptic plasticity, rTMS may prime the brain to be more receptive to subsequent cognitive and behavioral interventions in MCI. Among various forms of physical activity, dance stands out as a particularly rich, multi-faceted intervention for older adults with MCI. Dance—particularly structured forms such as Chinese square dancing—integrates physical, cognitive, social, and emotional components, offering benefits beyond conventional aerobic exercise (Colcombe and Kramer, 2003; Tao et al., 2023; Wu et al., 2022). It improves cardiovascular fitness, balance, gait speed, and motor coordination, all vital for maintaining physical independence and reducing fall risk in MCI (Sánchez-Alcalá et al., 2025). Learning and executing complex dance sequences demand continuous attention, working memory, planning, and decision-making, providing intensive cognitive training, while synchronizing movements to music and partners further challenges dual-tasking abilities and cognitive flexibility (Quan et al., 2025). Group dance activities foster social engagement and a sense of community—reducing loneliness and isolation, which are known risk factors for cognitive decline and depression in MCI (Cacioppo and Cacioppo, 2018)—while the accompanying music, rhythmic movements, and expressive elements can enhance mood, reduce stress, and provide multisensory input that supports brain health and emotional regulation (Hewston et al., 2021). Chinese square dancing, with its energetic rhythms and group format, is particularly well-suited to delivering these benefits, as it is easy to learn, affordable, and highly popular among older adults in China (Ou et al., 2022).

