### Intervention protocol

2.3

The study consists of a 12-week intensive intervention phase followed by a 12-week follow-up phase. This 12-week duration is chosen based on evidence that significant cognitive and neuroplastic changes in MCI populations typically manifest within 3 months of rTMS and structured exercise (e.g., dance) (Guo et al., 2025; Sánchez-Alcalá et al., 2025). While a 24-week intervention was considered, the 12-week model is preferred to maximize participant retention and minimize “intervention fatigue” in this elderly population, while still being sufficient to demonstrate synergistic effects (Ren et al., 2025). The subsequent 12-week follow-up will allow for the assessment of the durability of these effects—a critical factor for clinical translation. Participants will be supervised by trained instructors and medical staff.

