The dance moves are gender-neutral and applicable to both males and females. Dance routines will be adapted to participants’ abilities, and new routines may be introduced every three to four weeks. Each session will be led by one dance instructor positioned at the front of the group, who will lead the dance and encourage social connection. A second instructor and supporting medical staff will supervise participants’ movements, guide correct execution, and ensure safety. The DMI targets both motor participation and specific cognitive processes. At the motor level, the choreographed and improvised routines are designed to engage whole-body coordination, balance, and cardiovascular demand. At the cognitive level, the routines are designed to engage attention, working memory, motor planning, and executive function—through memorizing step sequences, synchronizing movements to music, adapting to changing choreographic patterns, and engaging in partner-based interactions. Participants are not required to perform movements with 100% accuracy; rather, the emphasis is on sustained engagement with both the motor and cognitive demands of the task, in order to experience the body as a source of creativity and reliability. A practice video featuring standard movements will be provided after each class to support at-home familiarization. Rest periods, during which participants may sit and drink water, are built into each session. To accommodate older participants, the dance intervention can be performed in seated positions when needed to reduce fatigue. Intervention fidelity and adequate involvement will be documented session-by-session using a structured adherence log completed by the supervising instructor. The log will capture: (i) session attendance and duration of active participation; (ii) instructor-rated movement engagement and quality on a 5-point Likert scale; (iii) proportion of the session completed in standing versus seated position; and (iv) any adverse events or safety concerns. These data will be used to characterize intervention delivery and to support per-protocol analyses.

Each dance class will consist of six structured components, delivered in the following sequence:

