-t₁: Initial screening phase to determine clinical eligibility based on MoCA, Geriatric Depression Scale (GDS-15), and Berg Balance Scale (BBS) inclusion criteria. T0: Baseline assessment conducted immediately prior to randomization. T1: Primary endpoint assessment conducted immediately following the 12-week intervention. T2: Follow-up assessment conducted 12 weeks post-intervention to determine durability of effects. MoCA, Montreal Cognitive Assessment; GDS-15, 15-item Geriatric Depression Scale; WMS-IV, Wechsler Memory Scale Fourth Edition; BBS, Berg Balance Scale; 6MWT, 6-Minute Walk Test; SF-12, 12-item Short Form Health Survey; EEG/ERP, Electroencephalography/Event-Related Potential; rs-fMRI, Resting-state Functional Magnetic Resonance Imaging.

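### The T0–T2 change labelled as durability does not separate retention from the size of the Week 12 gain, and dancing after Week 12 is not recorded, so it does not by itself test the 'more durable' hypothesis

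*Protocol article*

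**What the plan says.** Section 2.10 (Outcome hierarchy and multiplicity adjustment) attaches the word durability to a specific contrast, "T0 to T2 changes (durability) for all three key secondary outcomes", and says that these and the remaining outcomes "are treated as supportive/exploratory and are interpreted with caution".

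The follow-up phase is there for this question. Section 2.3 states: "The subsequent 12-week follow-up will allow for the assessment of the durability of these effects". The footnote to Table 1 says: "T2: Follow-up assessment conducted 12 weeks post-intervention to determine durability of effects". The Conclusions (section 4) then make the question comparative, expecting in the Combined arm "superior and more durable improvements in global cognition and physical performance compared to the monotherapy or control groups".

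The mixed model in section 2.9.1.2 has as fixed effects Group, "Time (T0, T1, T2), and the Group × Time interaction term". It therefore contains both T1 and T2, but no section names the T1–T2 change as a measure of durability.

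On activity after Week 12:
- The Introduction describes square dancing as "easy to learn, affordable, and highly popular among older adults in China".
- Section 2.3.2 adds for the dance arms: "A practice video featuring standard movements will be provided after each class to support at-home familiarization".
- The adherence log in the same section covers supervised sessions.
- The exercise restriction in section 2.2 looks back six months from entry.
- Table 1 lists no activity measure at T2.

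**The concern.** Superior and more durable are two different claims. Superiority at Week 12 concerns the size of the gain; durability concerns what happens to that gain once treatment ends. The T0–T2 change is the sum of the two. An arm that gained more by Week 12 can still be ahead at Week 24 while losing ground faster, and under the label in section 2.10 it could be reported as more durable.

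The second difficulty is what participants do in Weeks 13–24. Stimulation ends with the programme, because it needs the hospital's equipment. Dancing need not end. By design, 80 participants are taught to dance and given practice videos, and 80 are not. If some continue, a better Week 24 result in the dance arms could reflect carry-over from a finished course, continued dancing, or both, and nothing in the article would let a reader tell which.

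At stake is the wording of the durability conclusion, which section 2.3 treats as important for clinical translation.

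**Working it through.** **Inputs from the article.** Assessments at T0, T1 (Week 12) and T2 (Week 24); 160 randomised 1:1:1:1; 20% attrition over 24 weeks. 160 × (1 − 0.20) = 128, or 32 per arm, which agrees with section 2.7. The article gives no figure for durability, so the gains, retention, continuation rates, SDs and correlations below are assumptions for illustration.

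**1. What T0–T2 measures.** For each arm, (T0–T2 change) = (T0–T1 change) + (T1–T2 change).

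| Arm (assumed MoCA points) | T0–T1 | T0–T2 | T1–T2 | Share kept |
|---|---|---|---|---|
| Combined | +3 | +1.5 | 1.5 − 3 = −1.5 | 50% |
| DMI Only | +1 | +1 | 1 − 1 = 0 | 100% |
| Combined − DMI Only | +2 | +0.5 | −1.5 | |

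T0–T2 favours Combined by 0.5 points, while T1–T2 shows it losing 1.5 points more. Both are correct; they answer different questions.

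**2. T1–T2 alone is no better a test.** A Control arm that gains 0 and loses 0 has a T1–T2 change of 0, against −1.5 for Combined. On that contrast alone, an arm with no benefit would count as the more durable.

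**3. Continued dancing, dance against non-dance arms.** Assume a dance gain of 2 points at T1, half kept without further dancing and all kept with it. If a share q of the dance arms continues and nobody in the other arms starts, the Week 24 contrast is 2 × [q + 0.5(1 − q)] = 1 + q. True carry-over is 1.00.

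| q | 0% | 25% | 50% | 75% |
|---|---|---|---|---|
| Nobody in non-dance arms starts | 1.00 | 1.25 | 1.50 | 1.75 |
| 25% of non-dance arms start and gain 2 (subtract 0.25 × 2 = 0.50) | 0.50 | 0.75 | 1.00 | 1.25 |

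The contrast can lie above or below the carry-over.

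**4. Continued dancing, Combined against DMI Only.** With T1 gains of 4 and 2 and the same q in both arms, the Week 24 values are 4 × [q + 0.5(1 − q)] and 2 × [q + 0.5(1 − q)]. The share kept is (1 + q)/2 in both, so equal continuation does not distort relative retention. The gap in points does grow, from 2.0 − 1.0 = 1.0 at q = 0 to 3.5 − 1.75 = 1.75 at q = 75%. Relative retention is distorted only if continuation differs between the two arms. Section 3.2 makes that possible, since it hypothesises that stimulation may raise motivation and so adherence to dance.

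**5. Precision of the T1–T2 contrast.** Detectable difference between two arms, two-sided 5%, 80% power, 32 per arm: (1.960 + 0.842) × SD × √[2(1 − ρ)] × √(2/32).
- SD 3, ρ 0.7: 2.802 × 2.32 × 0.25 = 1.6 points. Power for a 1-point difference is 0.41.
- SD 2, ρ 0.8: 0.9 points.
- SD 4, ρ 0.5: 2.8 points.

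The contrast can be estimated from the planned visits, but not precisely.

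**The case against.** The strongest reply is that the benefit still present at Week 24 is an ordinary meaning of durable effect. T0–T2 is a valid randomised comparison of net benefit, including whatever people choose to do after the programme, and continued dancing may itself be a result of having been taught. The T1–T2 contrast needs no new data, and section 2.9.1.4 already foresees adjusted comparisons across groups or time points. The article marks these analyses as exploratory and states no rule for ranking arms on durability. All of this stands, and it is why T0–T2 should be kept and why T1–T2 should not replace it. It does not make T0–T2 a measure of retention, which the comparative hypothesis in the Conclusions calls for.

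A second reply is that activity questions are case-report-form detail that a condensed article may leave out. That is fair, and it makes this half of the point the weaker one. The nearest material in the article does not fill the gap: the discontinuation rule in section 2.2 concerns a needed additional intervention and does not name leisure dancing, and the Week 24 interviews reach only about 20–25 participants.

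A reader might go further and infer that the follow-up phase cannot support any durability conclusion. The documents do not support that. T1 and T2 are both measured and modelled, and equal continuation leaves relative retention in Combined against DMI Only undistorted.

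**Conclusion.** The point holds in limited form. T0–T2, as labelled in section 2.10, estimates the effect present at Week 24 and by itself does not test whether the combination is more durable. Separately, nothing in the article limits or records dancing or structured exercise in Weeks 13–24. Week 24 contrasts of the dance arms with rTMS Only and Control may therefore mix carry-over with continued dancing, and so may Combined against DMI Only if continuation differs.

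The size is not known. In the assumed examples the ranking reverses (+0.5 on T0–T2 against −1.5 on T1–T2), and a carry-over of 1.00 appears as anything from 0.50 to 1.75 points. These figures show direction and possibility; they do not predict this trial. The activity half also assumes that the full protocol does not already collect this information.

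The consequence is confined to exploratory durability statements. The primary outcome and the key secondary outcomes at T0–T1 are untouched. This is an inexpensive improvement to the plan and does not call the design into question.

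**What to change.** 1. For MoCA and the other outcomes measured at T2, keep the T0–T2 between-arm difference but describe it as the effect present at Week 24. Report the T1–T2 between-arm contrast from the same mixed model beside it, with 95% confidence intervals.
2. Claim greater durability only if T0–T2 favours the Combined arm and T1–T2 does not show greater loss there. Do not use T1–T2 alone. Because that contrast is imprecise, judge it on the estimate and interval; a non-significant p-value is not evidence of equal loss. State that loss is counted in points: an arm with a larger gain that keeps the same share loses more points, so give the share kept as description.
3. At T2, ask participants in all four arms how often they danced or did structured exercise since T1. The frequency in the exercise exclusion criterion (three or more times per week) is a ready threshold. Report by arm, and word the conclusion as after the supervised programme if the dance arms continued.
4. While editing the sentence in section 2.10, name MoCA at T2, which the hypothesis needs, and remove P300 from the T0–T2 list: sections 2.4 and 2.4.3 record it only at T0 and T1, so that change cannot be computed.

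The cost is one further contrast from a model already planned and one or two questions at an existing visit. The price is an imprecise T1–T2 estimate and possibly weaker durability wording. The questions should be in place before the first T2 visit, because activity is hard to reconstruct later.
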